### **12.3. Pain, analgesic use and QoL**

Pain frequency and intensity, and use of analgesic medications to treat SCD pain will be recorded by the subject in a daily eDiary. The duration of pain and number of subject reported “pain crisis” days will be determined from the eDiary. Post-dosing values will be compared to run-in values. If the subject does not have daily access to such a phone, s/he will be provided with a paper version of the application and encouraged to record his/her daily ratings on paper.

For questionnaires for which the study developers have provided guidelines for scoring in the presence of missing data, those guidelines will be followed. For other instruments, the number of questionnaires will be tallied for which a particular data item is missing.

### **12.4. Pulmonary Function**

PFTs in clinic include forced vital capacity (FVC), Forced expiratory volume in 1 second (FEV $_1$ ), Forced expiratory flow 25%-75%, (FEF $_{25-75}$ ) and peak expiratory flow (PEF) and will be performed in the clinic at screening run-in, after dosing on Day 0, monthly and EOS. Run-in and post dosing values will be correlated/associated with PK/PD for each dose cohort.

An improvement in FEV $_1$  or FEV $_1$ /FVC by 20% will be examined to assess the impact of infusional NKTT120 on these endpoints and these results will be presented as point estimates of proportion of subjects achieving target reduction, with 90% confidence intervals, for subjects within each of the dose level cohorts of the study. Mixed models will be explored to elucidate the tempo of changes in pulmonary function, controlling for subject and for cohort of study, as well as other potential covariates.

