### **5.3. Biologic activity and biomarker objectives**

To investigate the biologic activity of NKTT120, a number of clinical assessments will be performed. These assessments will be evaluated pre- and post-dosing at appropriate intervals and will be correlated with the PK/PD profile of NKTT120. They include:

- 
1. Clinical measures of SCD activity (e.g., leukocyte counts, hemoglobin, reticulocytes, platelets, LDH, CRP)
  2. Pain frequency and intensity and use of analgesics as recorded daily in an eDiary
  3. AHR and use of SABA, both recorded daily in an eDiary, and additional assessment of AHR determined by PFTs at clinic visits
  4. QoL as determined by PROMIS short form and ASCQ-Me questionnaires administered in the clinic

To explore the biologic effects of depletion of iNKT cells on biomarkers of inflammation, coagulation, endothelial activation, and a number of serum and cellular biomarkers will be assessed (e.g., IFN $\gamma$ , TNF $\alpha$ , IL-1 $\beta$ , IL-6, IL-8, F1+2, D-dimers, vWF, sPLA2 and sP-selectin) pre- and post-dosing at clinic visits. Results will be correlated with the PK/PD profile of NKTT120.

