### Escalation scheme

Five dose levels of NKTT120 will be assessed. Each dose level will be administered as a single ascending IV dose. The dose levels to be investigated are 0.001, 0.003, 0.01, 0.03 and 0.1 mg/kg.

A standard dose escalation Fibonacci 3+3 design will be employed. Initially, three subjects will be treated. If no subject experiences DLT, dosing will escalate. If one subject experiences DLT, 3 additional subjects will be treated at the current dose and escalation will occur only if no more than 1 of 6 subjects experiences DLT. If  $\geq 2$  of 3 - 6 subjects experiences DLT at the initial dose level of 0.001 mg/kg, then it may be de-escalated. The study continues until MTD has been determined, or the highest dose cohort is filled. If no MTD is reached, RDL will be determined based on the overall safety profile of NKTT120 and the duration of iNKT cell depletion. The RDL(s) for phase 2 will be determined by a dose that is at or below the highest dose tested which is associated with timing of iNKT cell recovery that allows dosing every 4-6 months in phase 2 studies. The dose-level cohort that represents the RDL will be expanded to 6 subjects to confirm the RDL. [Table 5](#) below provides the probability of dose escalation.

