### **12.6. Sample Size**

Sample size is determined by the 3+3 study design and the number of dose-level cohorts (up to 5 cohorts planned). Approximately 30 subjects will be dosed in the trial, with three to six subjects per cohort. The minimum sample size is 2 subjects. Enrollment through follow-up is estimated to require 18 months. Subjects who are enrolled, sign informed consent but do not receive NKTT120, will be replaced.

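### Section 12.4 correlates lung function with PK/PD inside each dose cohort of three to six subjects; one model pooled over cohorts would use the dose contrast that this sets aside

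*Protocol*

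**What the plan says.** Section 12.4 gives the PK/PD analysis of the clinic lung-function tests in one sentence: "Run-in and post dosing values will be correlated/associated with PK/PD for each dose cohort". It does not say whether each subject contributes one summary value or a series of time-matched values, or which PK/PD quantity the run-in values are paired with. The same section also plans mixed models for the time course, "controlling for subject and for cohort of study, as well as other potential covariates"; PK/PD is not named as a term.

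On cohort size, Section 12.6 states: "Approximately 30 subjects will be dosed in the trial, with three to six subjects per cohort". On dose, the escalation scheme in Section 12 states: "The dose levels to be investigated are 0.001, 0.003, 0.01, 0.03 and 0.1 mg/kg".

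Other places set no cohort limit. Section 5.3 says of the clinical assessments, which include lung-function tests at clinic visits: "These assessments will be evaluated pre- and post-dosing at appropriate intervals and will be correlated with the PK/PD profile of NKTT120". The statistical methods in the synopsis relate PK/PD to adverse events, pain scores and other endpoints, and describe trends across cohorts. Section 12.1 lists adverse events, pain, diary endpoints and biomarkers for PK/PD association, but not lung function.

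**The concern.** The objective in Section 5.3 is to learn whether biologic activity, including airway function, follows the PK/PD profile. Subjects in one cohort receive the same mg/kg dose, so with one exposure value per subject a within-cohort correlation sees only the between-subject scatter around that dose. The 100-fold dose range (0.1 / 0.001) lies between cohorts and plays no part. Three to six points then give a coefficient that may be large in either direction by chance, and up to five such coefficients would be reported.

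The sentence also refers to values, not changes. Raw FVC and FEV1 carry differences in lung size between subjects. Run-in lung function correlated with drug levels measured later cannot show a drug effect.

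**Working it through.** **1. The plan's own figure.** Five cohorts of six give 5 × 6 = 30, which matches Section 12.6. If every cohort stays at three, the total is 5 × 3 = 15. If only the RDL cohort is expanded to six (Section 6.2), it is 3 + 3 + 3 + 3 + 6 = 18. The protocol states no power or precision for this correlation, so there is nothing further to reproduce.

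**2. Where the exposure contrast lies.** Inputs: the five planned doses, and an assumed between-subject CV of exposure of 20–50% (not in the protocol).
- Variance of ln(dose) over the five doses: 2.652.
- Within-cohort variance of ln(exposure) = ln(1 + CV²): 0.039 at 20%, 0.223 at 50%.
- Between-cohort share: 2.652 / (2.652 + 0.039) = 99%, and 2.652 / (2.652 + 0.223) = 92%.

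**3. Stability of r in one cohort.** With three independent normal pairs and no association, r has density 1 / (π√(1 − r²)).
- Mean |r| = 2/π = 0.64.
- P(|r| > 0.8) = 1 − (2/π) arcsin(0.8) = 1 − 0.59 = 0.41.
- Section 12.4 attaches no test to the correlation. As a yardstick only, two-sided 0.10 needs |r| > 0.988 at n = 3 and > 0.729 at n = 6. At 0.05 the limits are 0.997 and 0.811.
- At n = 6 and r = 0.5, the Fisher 90% interval is tanh(0.549 ± 1.645/√3) = −0.38 to 0.90.
- If five cohorts were each judged at 0.10 with no effect, at least one would pass with probability 1 − 0.9⁵ = 0.41; at 0.05, 1 − 0.95⁵ = 0.23.

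**4. What pooling recovers.** Simulation of 40,000 trials: one exposure value per subject, log exposure = log dose + normal error, linear effect, five equal cohorts, two-sided 0.05. The pooled correlation ρ is an assumption. Ranges are over CV 20–50%.

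| Assumed pooled ρ | Subjects per cohort | Power, one cohort | Power, common slope adjusted for cohort | Power, pooled |
|---|---|---|---|---|
| 0.5 | 3 | 4.9–5.1% | 5.4–7.5% | 54% |
| 0.5 | 6 | 5.2–5.9% | 6.2–11.8% | 86% |
| 0.7 | 3 | 5.0–5.4% | 6.3–12.2% | about 93% |
| 0.7 | 6 | 5.5–7.7% | 8.5–26% | over 99% |

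A pooled ρ of 0.5–0.7 shrinks to 0.07–0.26 inside a cohort, so per-cohort power stays close to the 5% level. The adjusted column shows why adding an exposure term to a model that still controls for cohort would recover little under this pairing.

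**5. If serial values are paired instead.** Section 4.9 estimates a half-life of about 22 days. Assuming single-exponential decline, concentration in one subject falls 2^(90/22) ≈ 17-fold in 90 days and 2^(180/22) ≈ 290-fold in 180 days. Steps 2 to 4 do not describe that analysis.

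**The case against.** Four arguments on the other side have force.

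- **The cross-dose contrast survives elsewhere.** Section 5.3 and the synopsis plan PK/PD association without a cohort limit, and the synopsis describes trends across cohorts. A reader might infer from 12.4 that a real airway effect would be missed by the whole plan. The protocol does not support that. However, the trend paragraph in the synopsis names only peak expiratory flow among the lung measures, and 12.4 is the statistics section specific to lung function.
- **The pairing is open.** Lung function, PK and iNKT counts are all collected on Day 0, monthly and at end of study (Table 3), and Section 12 plans serial changes within subjects. Time-matched pairs would keep a large within-subject contrast in every cohort. This stands, and it makes the figures in steps 2 to 4 conditional.
- **Run-in values and change.** Sections 6.3.2.2 and 12 already define the endpoint as change from run-in. iNKT cells are measured at run-in, and a first-in-human drug is absent then, so run-in can be an unexposed anchor. A reader might infer that using run-in values is itself an error. It is one only if they are correlated with later drug levels as though they were an outcome.
- **No test or claim of power.** The 90% level in 12.4 belongs to the responder proportions. The power and multiplicity figures therefore illustrate how little the coefficients can tell; they are not error rates of a planned decision.

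It would also be too strong to say that a cohort analysis cannot detect anything: at n = 6, a true within-cohort correlation of 0.9 has 82% power at two-sided 0.05. The pooled benchmark assumes linearity in log exposure. Section 4.4 reports complete depletion by 24 hours in monkeys at every dose from 0.01 to 0.3 mg/kg, so a saturating relation is possible.

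**Conclusion.** The point holds as a weakness in one exploratory secondary analysis. Read with one exposure value per subject, the by-cohort correlation in 12.4 sets aside 92–99% of the variance of log exposure (assumed CV 20–50%) and leaves coefficients that at n = 3 average 0.64 in absolute size when nothing is there. The wording is narrower than Section 5.3 and the synopsis, and the mixed model in the same section does not clearly repair it.

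The size of the gain from pooling depends on assumptions outside the protocol: the pooled correlation, the CV and a common shape. The MTD/RDL decision is not affected. This is a cheap improvement to a stated method, not a flaw that threatens the trial.

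**What to change.** Reword the sentence in Section 12.4 as follows:

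- Relate change from run-in in FEV1, FVC, FEF25-75 and PEF to log exposure and to time-matched iNKT depletion in one model pooled over all cohorts, adjusted for the run-in value. Use a subject random effect for serial data and no cohort fixed effect in that model.
- State the pairing: which exposure measure, and at which visits.
- Use run-in only as the unexposed baseline, not as an outcome correlated with later drug levels.
- Keep by-cohort results as descriptive plots and listings, and use them to look for a non-linear or saturating relation.
- Align the wording with the synopsis, Section 5.3 and Section 12.1, adding lung function to the list in 12.1.

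The cost is a few lines of text and no new data. The pooled model assumes a common exposure-response shape across doses. Because cohorts enrol in sequence, its slope may also pick up drift over time. The by-cohort plots can check the shape, but they cannot separate drift from dose.

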### **12.5. Immunogenicity Analysis**

The presence of ADA will be described as present or absent at each test. The percentage of positive tests will be reported for each dose cohort and the study as a whole.

### **12.6. Sample Size**

Sample size is determined by the 3+3 study design and the number of dose-level cohorts (up to 5 cohorts planned). Approximately 30 subjects will be dosed in the trial, with three to six subjects per cohort. The minimum sample size is 2 subjects. Enrollment through follow-up is estimated to require 18 months. Subjects who are enrolled, sign informed consent but do not receive NKTT120, will be replaced.

### **12.7. Reporting and Exclusions**

Evaluation of toxicity will be as follows:

All subjects who initiate infusion with NKTT120 will be evaluable for adverse events from the time of enrollment.

## **13. DIRECT ACCESS TO SOURCE DATA/DOCUMENTS**

### **13.1. Study Monitoring**

Before an investigational site can enter a subject into the study, a representative of NKTT will visit the investigational study site to:

- Determine the adequacy of the facilities
- Discuss with the investigator(s) and other personnel their responsibilities with regard to protocol adherence, and the responsibilities of NKTT or its representatives. This will be documented in a Clinical Study Agreement between NKTT and the investigator.

During the study, a monitor from NKTT or sponsor representative will have regular contacts with the investigational site, for the following:

- Provide information and support to the investigator(s)
- Confirm that facilities remain acceptable
- Confirm that the investigational team is adhering to the protocol, that data are being accurately recorded in the electronic case report forms, and that investigational product accountability checks are being performed
- Perform source data verification. This includes a comparison of the data in the case report forms with the subject's medical records at the hospital or practice, and other records relevant to the study. This will require direct access to all original records for each subject (e.g., clinic charts)
- Record and report any protocol deviations not previously sent to NKTT
- Confirm AEs and SAEs have been properly documented on eCRFs and confirm any SAEs have been forwarded to NKTT and those SAEs that met criteria for reporting have been forwarded to the IRB

The monitor will be available between visits if the investigator(s) or other staff needs information or advice.

### **13.2. Audits and Inspections**

Authorized representatives of NKTT, a regulatory authority, an Independent Ethics Committee or an Institutional Review Board may visit the site to perform audits or inspections, including source data verification. The purpose of an NKTT audit or inspection is to systematically and independently examine all study-related activities and documents to determine whether these activities were conducted, and data were recorded, analyzed, and accurately reported according to the protocol, Good Clinical Practice guidelines of the International Conference on Harmonization, and any applicable regulatory requirements. The investigator should contact NKTT immediately if contacted by a regulatory agency about an inspection.

---

### **13.3. Institutional Review Board (IRB)**

The Principal Investigator must obtain IRB approval for the investigation. Initial and annual IRB approval, protocol amendment approval and all materials approved by the IRB for this study including the subject informed consent form and recruitment materials must be maintained by the Investigator and made available for inspection.

## **14. QUALITY CONTROL AND QUALITY ASSURANCE**

To ensure compliance with Good Clinical Practices and all applicable regulatory requirements, NKTT or representative may conduct a quality assurance audit. Please see Section [13.2](#) for more details regarding the audit process.

## **15. ETHICS**

### **15.1. Ethics Review**

The final study protocol, including the final version of the Informed Consent Form, must be approved or given a favorable opinion in writing by an IRB as appropriate. The investigator must submit written approval to NKTT before he or she can enroll any subject into the study.

The Principal Investigator is responsible for informing the IRB of any amendment to the protocol in accordance with local requirements. In addition, the IRB must approve all advertising used to recruit subjects for the study. The protocol must be re-approved by the IRB upon receipt of amendments and annually, as local regulations require.

The Principal Investigator is also responsible for providing the IRB with reports of any reportable serious adverse drug reactions from all studies conducted with the investigational product. NKTT will provide this information to the Principal Investigator.

Progress reports and notifications of serious adverse drug reactions will be provided to the IRB according to local regulations and guidelines.

### **15.2. Ethical Conduct of the Study**

The study will be performed in accordance with ethical principles that have their origin in the Declaration of Helsinki (Section [18.3](#)) and are consistent with ICH/Good Clinical Practice, applicable regulatory requirements.

### **15.3. Written Informed Consent**

The Principal Investigator(s) at each center will ensure that the subject is given full and adequate oral and written information about the nature, purpose, possible risk and benefit of the study. Subjects must also be notified that they are free to discontinue from the study at any time. The subject should be given the opportunity to ask questions and allowed time to consider the information provided.

All subjects (or their legally acceptable representative) must read, sign, and date a consent form before any assessments for participating in the study, taking the study drug, and/or undergoing any study-specific procedures. If a participant does not speak and read English, the consent materials must be translated into the appropriate language. A copy of the informed consent form will be given to the subject and the original will be placed in the subject's medical record if in accordance with the institution's standard operating procedures. An entry must also be made in the subject's chart to confirm that informed consent was obtained prior to any study-related procedures and that the subject received a signed copy.

The informed consent form must be updated or revised whenever important new safety information is available, whenever the protocol is amended, and/or whenever any new information becomes available that may affect participation in the trial.

A copy of the informed consent will be given to a prospective participant for review. The investigator, in the presence of a witness, will review the consent and answer questions. The

participant will be informed that participation is voluntary and that he/she may withdraw from the study at any time, for any reason.

The Principal Investigator(s) must maintain the original, signed Informed Consent Form. A copy of the signed Informed Consent Form must be given to the subject.

#### **15.4. Confidentiality of Subject Records**

Subject information collected in this study will comply with the standards for protection of privacy of individually identifiable health information as promulgated by applicable local/regional/national requirements for subject confidentiality (e.g., Health Insurance Portability and Accountability Act as mandated in Title 45 CFR, Parts 160 and 164). All records will be kept confidential and the subject's name will not be released at any time. Subject records will not be released to anyone other than NKTT or its designee(s), and responsible government agencies, when requested. In all cases, caution will be exercised to assure the subject's confidentiality. Datasets for each subject will be identified by a unique number.

#### **15.5. Financial Disclosure**

In compliance with 21 CFR Part 54, any listed or identified investigator or subinvestigator (including the spouse and any dependent children of said individuals) directly involved in the treatment or evaluation of research subjects will disclose the following information for the time period during which the investigator is participating in the study and for one year following completion of the study:

1. Any financial arrangement entered into between the Sponsors and the investigator, whereby the value of the compensation to the investigator for conducting the study could be influenced by the outcome of the study;
2. Any other significant payments totaling > \$25,000, exclusive of the costs of conducting this or other clinical studies, by the Sponsors, such as a grant to fund ongoing research, compensation in the form of equipment, retainer for ongoing consultation, or honoraria;
3. Any proprietary interest in the product being evaluated;
4. Any significant equity interest, including ownership interest, stock options, or other financial interest whose value cannot be determined through reference to public prices or any equity interest in NKTT that exceeds \$50,000.

## **16. DATA HANDLING AND RECORDKEEPING**

### **16.1. Inspection of Records**

NKTT or representative will be allowed to conduct site visits to the investigation facilities for the purpose of monitoring any aspect of the study. The Investigator agrees to allow the monitor to inspect the drug storage area, study drug stocks, drug accountability records, subject charts and study source documents, and other records relative to study conduct.

### **16.2. Retention of Records**

The Principal Investigator must maintain all documentation relating to the study for a period of 2 years after the last marketing application approval, or if not approved 2 years following the discontinuance of the test article for investigation. If it becomes necessary for NKTT or the Regulatory Authority to review any documentation relating to the study, the Investigator must permit access to such records.

### **16.3. PUBLICATION POLICY**

The information obtained during the conduct of this clinical study is confidential, and disclosure to third parties other than those noted below is prohibited. All information concerning the product as well as any matter concerning the operation of the Sponsor, such as clinical indications for the drug, its formula, methods of manufacture and other scientific data relating to it, that have been provided by the Sponsor and are unpublished, are confidential and must remain the sole property of the Sponsor. The investigator will agree to use the information only for the purposes of carrying out this study and for no other purpose unless prior written permission from the Sponsor is obtained.

Information obtained during the conduct of this study will be used by NKTT in connection with the development of the study drug. The study Investigator is obliged to provide NKTT with complete test results and all data developed in this study. The Sponsor has full ownership of the original case report forms completed as part of the study. This information may be disclosed to other physicians who are conducting similar studies and to the FDA as deemed necessary by the Sponsor. Subject specific information may be provided to other appropriate medical personnel related to the care of that subject only with subject's prior consent.

To ensure compliance with current Federal Regulations and the ICH guidelines, data generated by this study must be available for inspection upon request by representatives of the FDA and other regulatory agencies, national and local health authorities, NKTT and the IRB for each study site.

The Publication Committee (PC) will be responsible for preparing and submitting the primary clinical publication arising from this study. The membership for this committee consists of the Principal Investigator(s) and co-investigators, and NKTT designee. Any additional presentations and publications arising from the study must also be approved by the PC, which will undertake to review such publications within 30 days of receipt. Authorship for all presentations and publications will be decided by the PC, based on contributions to study concept, design and

---

execution. Subject names and other identifiers, such as photographs, audio or videotapes, may not be disclosed in any publication without prior written authorization from the subject.

